## Abstract

**Introduction:**

Patients with paediatric-onset inflammatory bowel disease (PIBD) may develop a complicated disease course, including growth failure, bowel resection at young age and treatment-related adverse events, all of which can have significant and lasting effects on the patient’s development and quality of life. Unfortunately, we are still not able to fully explain the heterogeneity between patients and their disease course and predict which patients will respond to certain therapies or are most at risk of developing a more complicated disease course. To investigate this, large prospective studies with long-term follow-up are needed. Currently, no such European or Asian international cohorts exist. In this international cohort, we aim to evaluate disease course and which patients are most at risk of therapy non-response or development of complicated disease based on patient and disease characteristics, immune pathology and environmental and socioeconomic factors.

**Methods and analysis:**

In this international prospective observational study, which is part of the PIBD Network for Safety, Efficacy, Treatment and Quality improvement of care (PIBD-SETQuality), children diagnosed with inflammatory bowel disease <18 years are included at diagnosis. The follow-up schedule is in line with standard PIBD care and is intended to continue up to 20 years. Patient and disease characteristics, as well as results of investigations, are collected at baseline and during follow-up. In addition, environmental factors are being assessed (eg, parent’s smoking behaviour, dietary factors and antibiotic use). In specific centres with the ability to perform extensive immunological analyses, blood samples and intestinal biopsies are being collected and analysed (flow cytometry, plasma proteomics, mRNA expression and immunohistochemistry) in therapy-naïve patients and during follow-up.

**Ethics and dissemination:**

Medical ethical approval has been obtained prior to patient recruitment for all sites. The results will be disseminated through peer-reviewed scientific publications.

**Trial registration number:**

NCT03571373.

Strengths and limitations of this studyInternational prospective observational study with long-term follow-up examining clinical phenotype and biomarkers that may be predictive for complicated disease course, serious adverse events and response (or not) to therapy.The ability to perform extensive immunological analysis (eg, flow cytometry, plasma proteomics, messenger RNA expression and immunohistochemistry) of peripheral blood leucocytes and biopsies in therapy-naïve patients to evaluate heterogeneity at diagnosis and to follow-up these immunological parameters during disease course and therapy use.The first prospective PIBD cohort that includes patients from several European and some Asian countries, which enables comparison of therapeutic strategies between countries and continents, and outcomes of these strategies.Large scale collection of quality of life measures (eg, IMPACT III and EQ-5D questionnaires) to correlate to clinical findings and compare this across countries and ethnicities.Different methods between centres for measurement of laboratory parameters that are part of standard clinical care serve as a limitation to this study.

## Introduction

### Background

Paediatric-onset inflammatory bowel disease (PIBD) is a chronic disease that often leads to disabling symptoms such as abdominal pain, diarrhoea and rectal bleeding. Inflammatory bowel disease (IBD) comprises Crohn’s disease (CD), ulcerative colitis (UC) and IBD unclassified (IBD-U). Although IBD is most frequently known as an adult disease, in 5%–25% of cases, it is diagnosed during childhood or adolescence.^1–3^ The incidence of IBD in Western Europe and North America ranges from 1.85 to 23.82 per 100 000 for CD and 1.9 to 23.14 per 100 000 for UC.^4^ Despite the fact that the incidence of IBD varies among different countries, a current concern is that the general trend shows increasing incidence rates over recent decades, especially among the patients <10 years of age.^1 3 5–7^ Compared with adult-onset IBD, PIBD reflects a more severe disease.^8–10^ Consequences of the disease, such as growth failure and bowel resection at a young age, may have a large impact on the patient’s further development and quality of life (QoL). In addition, the early onset of this disease regularly leads to an early use of intensive therapies with a life-long risk of treatment-related adverse events.^8 11–13^

The pathogenesis of PIBD is currently partly explained by a combination of a genetic predisposition, microbial factors and susceptibility of the immune system leading to an aberrant inflammatory immune response.^14–16^ Treatment strategies therefore focus on modulating or suppressing the immune response using immunosuppressive drugs or biologicals. Despite the known heterogeneity within paediatric patients with CD and UC at both disease diagnosis and during follow-up, we are still not able to predict which patients are at risk of developing a complicated disease course and which patients will respond to therapy.^17 18^ Therefore, the majority of patients with PIBD have been treated following a step-up approach, a strategy in which patients start with a simpler, easily available therapy at the bottom of the therapeutic pyramid and medications at the top are often considered more efficacious but may present greater risk to the patient. This approach may lead to a delay in treatment response and increases the risk of ongoing inflammation risking penetrating and stricturing complications. The ability to predict complicated disease course and response or non-response to therapy would be of immense value. This is essential to develop strategies that balance, on an individual basis, therapeutic effectiveness with risks of treatment.

In studies including adult patients with IBD, several clinical risk factors have been identified for the development of a complicated disease course in CD and the need for colectomy in patients with UC.^19 20^ Given the differences in disease phenotype, course of disease and benefits and risks of treatment between children and adults, findings from studies in adult patients with IBD do not directly apply to PIBD. Few studies have assessed risk factors in patients with paediatric-onset CD and found that both stricturing disease behaviour^17 21 22^ and older age at diagnosis^23–25^ are associated with an increased risk for the need for surgery. In patients with paediatric-onset UC, the Paediatric Ulcerative Colitis Activity Index (PUCAI) at diagnosis and 3 months after diagnosis is found to be an essential predictor of colectomy.^26 27^ Kugathasan *et al* demonstrated that early anti-tumour necrosis factor (TNF) therapy in CD was associated with a decreased risk of penetrating but not stricturing complications.^28^

Due to the small number of available studies comprising a large variety of data on several different outcomes and predictors combined with a mainly retrospective set-up, to date, most findings regarding predictors of disease course in PIBD are inconclusive. The majority of the identified predictors are demographic or associated with the disease phenotype, and studies lack findings on the predictive value of biomarkers. Despite the known role of the immune system in PIBD, no immunological biomarkers have been identified to correlate with the disease phenotype or disease course. Therefore, there is an urgent need to generate a prospective long-term real-world cohort designed to analyse effectiveness and safety signals with the ability to correlate them to individual risk factors in well-phenotyped patients. To address this issue, the Paediatric Inflammatory Bowel Diseases Network for Safety, Efficacy, Treatment and Quality (PIBD-SETQuality) inception cohort was designed. Besides a few prospective PIBD cohorts, established in the USA and Canada, no international European cohorts currently exist to assess this.^28^ Due to possible differences in genotype, environmental influences and treatment algorithms, European data are required. With this paper, we aim to inform the IBD research community about the existence of the PIBD-SETQuality inception cohort and provide insight into the establishment of this cohort.

### Objectives

PIBD-SETQuality is an international project with the overall goal to develop and validate a treatment algorithm for PIBD based on high-risk or low-risk predictors for early complicated or relapsing disease. In this inception cohort, predictors of disease course are identified through prospective collection of longitudinal PIBD data in the first cohort that includes patients from several European and some Asian centres. Table 1 depicts the potentially relevant prognostic factors listed by the consortium, which formed the basis of parameters to investigate in this study.

**Table 1 T1:** Potentially relevant prognostic factors in prediction of disease course and therapy responsiveness in PIBD

Potentially relevant prognostic factors	
1	Family history
2	Medical history
3	Ethnicity
4	Severity of disease at diagnosis
5	Disease localisation
6	Course of disease
7	Level of inflammatory markers
8	Faecal calprotectin level
9	Endoscopic findings
10	Immunological biomarkers
11	Genetic polymorphisms
12	Environmental factors
13	Dietary factors
14	Health economic status
15	Psychosocial status

The main objective of this study is to facilitate the discovery of predictors of disease course, treatment response or non-response and severe adverse events in patients with PIBD by:

Collecting real-world longitudinal data with preferably a 20-year follow-up period.Collecting biomaterials and linking this to the detailed clinical data.Using standardised questionnaires to assess QoL.

In addition, this cohort enables investigation of PIBD heterogeneity based on immunological biomarkers and racial or environmental factors. Patients of differing ethnicities in the European countries will be included along with patients from some non-European countries, which can allow comparison of different races in immigrant and non-immigrant subgroups.

## Methods and analysis

### Study design

The PIBD-SETQuality inception cohort is a multicentre prospective observational study in patients with PIBD. Participants are followed from the moment of diagnosis up to 20 years thereafter. During the first year after diagnosis, data collection is performed more frequently and reduced to annual visits after the second year of follow-up (table 2).

**Table 2 T2:** Visit schedule and included activities for PIBD-SETQuality inception cohort

Visit number	Visit 0	Visit 1	Visit 2	Visit 3	Visit 4	Visit 5	Annual visits	Unscheduled visit
Time point	Prior to start of therapy	4 weeks after start of therapy	3 months after start of therapy	6 months after start of therapy	12 months after start of therapy	18 months after start of therapy	24, 36 months and so on	
**Activity**								
Study explained, informed consent	X							
Collection of routine clinical and laboratory data, including faecal calprotectin	X	X	X	X	X	X	X	X
Extra blood sample taken at time of routine blood draw (maximum of 20 mL)*****	O	O	O	O	O	O	O	O
Extra biopsies taken at time of clinically required colonoscopy (maximum of 8)*	O							O
Tissue sample in case of indication for surgical resection*		O	O	O	O	O	O	O
Environmental questionnaire	X							
IMPACT III and EQ-5D questionnaires	X (both)		X (EQ-5D)	X (EQ-5D)	X (both)	X (EQ-5D)	X (both)	
School attendance and WPAI questionnaires	X (both)		X (both)		X (both)		X (both)	

*This activity will only be performed in patients included in the subcohort. ‘X’ is performed in all patients, ‘O’ is only performed in patients included in the subcohort.

WPAI, Work Productivity and Activity Impairment.

At least 535 patients with PIBD need to be included in the inception cohort. However, since this is an observational study, depending on the feasibility, the study will aim to recruit 1000 patients. In specific centres with the capacity to perform immunological analyses, participants are included in a subcohort for additional collection of biological specimens. This allows in-depth characterisation of immunological pathways in 100 patients with CD and 50 patients with UC and provides the opportunity to relate predictive factors to underlying immune dysfunction during follow-up. The inception cohort is part of the PIBD-SETQuality project, which is funded by Horizon 2020.

### Eligibility criteria

Children and adolescents <18 years with a likely or confirmed diagnosis of IBD are eligible. Diagnosis has to be made or confirmed within the first 2 months after inclusion. Diagnosis must be based on history, physical examination, laboratory, endoscopic, radiological and histological features according to the revised Porto criteria.^29^ If a diagnosis of IBD is not confirmed after the investigations are complete, the patient will be excluded from follow-up. Other inclusion criteria comprise available data on all diagnostic procedures for inclusion in the database, informed consent of patient and parents according to the national guidelines, and in case of inclusion in the subcohort for collection of biomaterial, the patient has not started therapy yet at the moment of diagnostic endoscopy. Patients are excluded from this study: (1) when they are on similar treatments as for IBD but for other conditions, defined as the use of any biological, immunosuppressant or systemic corticosteroid; (2) when they are known to have conditions directly affecting IBD (eg, immunodeficiency or major gastrointestinal resections); and (3) in case of inability to read or understand the patient and family information sheets.

### Recruitment and data collection

All eligible patients are asked for informed consent to participate in the inception cohort. Within this study, clinical data and results of questionnaires will be collected in all patients. Biomaterial is collected as part of the subcohort in specific centres with the ability to perform immunological analyses.

#### Clinical data

At baseline, data on demographics, family history, diagnosis, disease activity, disease localisation and results of physical examination, endoscopy, radiographic imaging and laboratory results, including faecal calprotectin levels, are collected. Validated scores and classifications such as the weighted Paediatric Crohn’s Disease Activity Index (wPCDAI), PUCAI, Simple Endoscopic Score for Crohn’s Disease and Ulcerative Colitis Endoscopic Index of Severity are used.^30–33^ During follow-up, the clinical disease activity scores, results of additional investigations and detailed treatment information are collected at fixed time points and during hospitalisations.

#### Questionnaires

To assess the QoL, the validated IMPACT III questionnaire is being used. This questionnaire is a disease-specific health-related assessment of QoL, divided in the domains emotional functioning, social functioning, body image and well-being.^34 35^ Validated EQ-5D questionnaires are being used to assess the health status of the patient (EQ-5D-Y and EQ-5D-Y proxy) and the parents (EQ-5D-5L). The EQ-5D questionnaire consists of five dimensions: mobility, self-care, usual activities, pain/discomfort and anxiety/depression.^36^ Parent’s work productivity is assessed by the Work Productivity and Activity Impairment questionnaire (WPAI) for caregivers. All validated questionnaires are used in accordance with their respective instructions regarding age limits. If validated translations of the IMPACT III, EQ-5D and WPAI are not available in a certain language, patients in the respective country will not complete these questionnaires. Due to the lack of validated questionnaires assessing the child’s school attendance, a non-validated questionnaire is being used to address this subject. The frequency of the assessment of these questionnaires is shown in table 2. At baseline, many environmental factors are being assessed comprising, for example, parent’s smoking behaviour, antibiotic use, sun exposure, previous enteritis and appendectomy. Assessment of dietary factors is limited to assessing: (1) whether children are following a vegetarian or vegan diet and (2) if they are excluding specific items from their diet.

#### Biomaterial

In several centres, biological specimens are collected in addition to the clinical data. When informed consent for the collection of biomaterial is obtained, blood samples and intestinal biopsies are collected prior to treatment initiation and during follow-up visits in concurrence with routine clinical diagnostics. At diagnosis, in all patients, biopsies are collected from affected and non-affected tissue in both ileum and colon according to the standard operating procedure written for this study (online supplementary figure 1). During follow-up endoscopies, collection of ileum biopsies is optional and based on the clinician’s decision in patients with UC. Analyses of biopsies include immunohistochemistry, targeted quantitative messenger RNA (mRNA) analyses and unbiased mRNA sequencing analyses. Peripheral blood samples are collected for plasma proteomics analyses, plasma antimicrobial reactivity, in-depth phenotypic and functional leucocyte analyses and screening for genetic polymorphisms (figure 1). Immunological analyses will be related to the previously described clinical data that is being collected. Patients enrolled in the subcohort in whom the diagnosis of IBD is not confirmed after additional investigations will be analysed as non-IBD controls.

10.1136/bmjopen-2019-035538.supp1Supplementary data

**Figure 1 F1:**
[figure not shown]
Different immunological analyses that will be performed. Data will be correlated to the clinical data. IHC, immunohistochemistry; ISH, in situ hybridisation.

### Outcome measures

This study design and statistical analysis plan are based on one primary and several secondary and exploratory outcomes. At baseline, prior to the start of therapy, the clinical characteristics of patients with PIBD will be reviewed and compared by country, as well as racial background. In patients participating in the subcohort, immunological biomarkers are reviewed in order to classify disease heterogeneity based on underlying immune pathology. Thereto, immunological parameters will be related to clinical and morphological disease features at this time point.

The primary outcome is clinical remission at 1 year, which reflects our aim to study therapy response and non-response. Clinical remission is defined as a wPCDAI <12.5 in patients with CD and a PUCAI <10 in patients with UC or IBD-U. According to the set hypothesis, the disease localisation, extension, behaviour and type of induction therapy are important factors that influence the primary outcome, while age at diagnosis and the initial disease activity score are expected to be important covariates. In addition, biochemical and immunological parameters at baseline will be evaluated to predict clinical remission. In a subanalysis, the effect of early use of immunomodulators and biologicals (less than 3 months from diagnosis) on remission rates will be investigated by comparing groups with early and later use.

One of the secondary outcomes of this study is to assess clinical remission over a period of 3 and 6 months since the start of treatment to evaluate short-term response. In addition, the need for treatment intensification within 1 year will be assessed. The longitudinal follow-up analyses of individual immunological biomarkers will reveal which immune parameters change when patients are in clinical remission. Clinical, biochemical and immunological findings at baseline and 12 weeks after the start of therapy will be assessed for their predictive value on the disease course after 1, 3, 5, 10, 15 and 20 years of follow-up. Lastly, as a longer term secondary outcome, we will assess: (1) moderate or severe disease over the last 6–12 months, (2) the development of complications such as fibrostricturing disease, penetrating disease, active perianal fistula or an abscess, (3) the need for IBD-related luminal surgery and (4) the need for biological use or need for treatment intensification, after 1, 3, 5, 10, 15 and 20 years.

As an exploratory outcome, the initial management of newly diagnosed patients with PIBD will be evaluated. The type of induction therapy and proportion of patients started on early immunomodulators or anti-TNF agents will be assessed and compared by country or region. Several environmental factors will be evaluated to assess their possible role in the heterogeneity of the presenting phenotype as well as disease course. Lastly, longitudinal findings on QoL, health status, parents’ work productivity and child’s school attendance will be evaluated, compared by country or region and correlated to disease activity and disease course.

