### Analysis and statistical methods

Data analysis will be performed with SPSS V.26 or higher for Windows and R version 3.6 or higher (R Foundation for Statistical Computing, Vienna, Austria). Descriptive statistics will be computed overall and per disease (CD and UC). Phenotypic grouping will be performed according to specific disease characteristics (eg, age of onset, disease localisation and disease behaviour). Next to this, patients will be categorised according to treatment categories. The appropriate descriptive statistics will be used to summarise the demographic characteristics. The primary outcome will be analysed using a 2-proportion Z test for the comparison of the different groups in our sample, using a stricter confidence level of 0.01 per Bonferroni correction. All proportions will be summarised per group, and 95% CIs will be provided. The important factors from the univariate analysis will be used to build a generalised linear model with a logit link function. This will be a multiple analysis of the effects that the selected factors and covariates have on the outcome of clinical remission. The final model will also include interaction terms, if necessary, and will be optimised based on fit diagnostics and residual analysis. The same approach will be used for the secondary outcomes of clinical remission. We will use a mixed-effects linear model to study the effects of the predictors on the disease activity index over time, taking into account the non-independence between the observations due to the repeated measurements from each patient. For the additional long-term secondary outcomes that have a time-to-event nature, we will use Kaplan-Meier curves to summarise the effects of the categorical factors on the outcome. This will be used to build a Cox regression model with the important factors and covariates that have a significant effect on the time and frequency of the events as defined in the outcomes section.

Similar methods will be used for the analysis of the exploratory outcomes. For these outcomes, propensity scores and multivariate methods are required, in particular for the immunological data, including principal component, factor and cluster analysis. Incidences of serious adverse events (SAE) and the SAE rate per 100 patient-years will be calculated. Missing data analysis will be performed based on the missing at random or missing completely at random mechanisms. Emerging patterns will be thoroughly examined.

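### The early-versus-later subanalysis forms its groups from treatment started after baseline and gives never-users no place, so its result cannot be read as the effect of early use

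*Protocol article*

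**What the plan says.** The Outcome measures section of the protocol article describes a subanalysis of "early use of immunomodulators and biologicals (less than 3 months from diagnosis"; the effect of such use "on remission rates will be investigated by comparing groups with early and later use". The sentence follows the definition of the main endpoint, "The primary outcome is clinical remission at 1 year", so 1-year remission is the natural reading of the outcome. The text does not say where patients who never start either drug class are counted.

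Two other places bear on this:

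- **Treatment pattern.** The Background says that "the majority of patients with PIBD have been treated following a step-up approach". Outcome measures also lists treatment intensification within 1 year, and the need for biologicals, among the secondary outcomes.
- **Adjustment.** Outcome measures states that "age at diagnosis and the initial disease activity score are expected to be important covariates". Analysis and statistical methods gives, for the primary outcome, a "2-proportion Z test for the comparison of the different groups in our sample", followed by a logit model with selected factors and covariates. Propensity scores appear in the paragraph on the exploratory outcomes: "For these outcomes, propensity scores and multivariate methods are required".

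**The concern.** The aim is causal (the effect of early use), but the comparator is identified by something that happens after the 3-month cut. On a plain reading, a patient who responds to first treatment and never needs an immunomodulator or biological is neither an early nor a later user. Under step-up care, the patients who do become later users tend to be those whose first treatment was not enough. The comparator is then partly selected on an event that the protocol elsewhere counts as an outcome, while the early group is not selected in this way.

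Adjustment for baseline covariates cannot repair this, because the selection acts through response after baseline. At stake is a result that clinicians would read as evidence on the timing of intensive therapy.

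**Working it through.** **The plan's own figures.** The article gives no sample size or expected rate for this subanalysis. The overall minimum follows from its inputs (214 / 0.40 = 535) and does not depend on the point made here. The only yardstick is the 25-point difference in Sample size calculation.

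**Inputs.** The documents give no remission or uptake rates, so every rate below is an assumption. In all scenarios the drugs have no effect on remission, whenever they are started.

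**Step 1: selection alone, by hand.** Let a share a = 0.60 respond by 3 months, with 1-year remission y1 = 0.75 in responders and y0 = 0.40 in non-responders. Early use is unrelated to prognosis. Among patients not treated early, r1 of responders and r0 of non-responders start later.

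- Early: a·y1 + (1-a)·y0 = 0.45 + 0.16 = 0.61
- Later: [a·r1·y1 + (1-a)·r0·y0] / [a·r1 + (1-a)·r0]

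| r1 / r0 | Later users | Early minus later |
|---|---|---|
| 0.15 / 0.70 | (0.0675 + 0.112) / 0.37 = 0.485 | +12.5 points |
| 0.30 / 0.70 | (0.135 + 0.112) / 0.46 = 0.537 | +7.3 |
| 0.50 / 0.70 | (0.225 + 0.112) / 0.58 = 0.581 | +2.9 |
| 0.70 / 0.70 | 0.610 | 0.0 |

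In the first row never-users remit at (0.3825 + 0.048) / 0.63 = 0.683. Putting them back gives 0.37·0.485 + 0.63·0.683 = 0.61, the early rate. The difference comes entirely from leaving them out.

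**Step 2: adding confounding by severity.** A simulation with 1,000,000 patients per scenario used baseline severity S ~ N(0,1) and these log-odds:

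- early start: -0.2 + c·S
- 3-month response R: 0.4 - 0.8·S
- 1-year remission: -0.4 + 1.5·R - 0.5·S

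Here c is the strength with which sicker patients are started early. Crude early-minus-later differences, in points:

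| r1 / r0 | c = 0 | 0.5 | 1.0 | 1.5 | 2.0 |
|---|---|---|---|---|---|
| 0.15 / 0.70 | +14.5 | +7.3 | +1.2 | -2.9 | -5.5 |
| 0.30 / 0.70 | +8.4 | +1.0 | -5.0 | -9.0 | -11.5 |
| 0.50 / 0.70 | +3.2 | -4.1 | -9.8 | -13.5 | -16.2 |

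With c = 0 in the first row, remission is 59.8% in early, 45.4% in later and 68.5% in never users.

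**Step 3: does baseline adjustment help, and does the other comparator help?** Same simulation, 0.15 / 0.70 row, stratified on true S in 20 strata:

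| Contrast | c = 0 | 0.5 | 1.0 | 1.5 | 2.0 |
|---|---|---|---|---|---|
| Early vs later, stratified | +10.7 | +10.7 | +10.4 | +10.3 | +10.3 |
| Early vs all not-early, crude | 0.0 | -7.2 | -13.0 | -16.7 | -19.2 |
| Early vs all not-early, stratified | 0.0 | 0.0 | -0.2 | -0.3 | -0.6 |

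Stratifying removes only the part of the selection that runs through baseline severity. About 10 points remain here, about 6 in the 0.30 / 0.70 row and about 2 in the 0.50 / 0.70 row. Early versus all not-early is close to zero once severity is adjusted for, but not before. Both the comparator and the adjustment are needed.

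**The case against.** The strongest reply is that this is one sentence on a subanalysis in a condensed article. It neither excludes never-users nor says that later use means only patients who eventually started. A fuller document may count them as not-early, which would remove the selection. That stands: a reader might infer that the plan deliberately drops never-users, and the text does not say so. What remains is that the article names its comparator, and its plain meaning has no place for these patients.

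A reader might also infer that the contrast must favour early use. The documents do not support that. The selection component points that way, but if sicker patients are treated early, confounding by indication can offset or reverse it, as step 2 shows. For the same reason early users should not be assumed to be unselected.

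Nor can one infer that confounding is ignored. Age and initial activity are named as covariates, and a logit model follows the Z test for the primary outcome. Naming propensity scores for the exploratory outcomes does not rule out adjustment here. Step 3 shows, however, that adjustment does not cure the comparator.

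Finally, the step-up remark describes past practice, and the article treats early uptake in this cohort as something to be measured. How strongly later start depends on response is therefore unknown. If it did not depend on it at all, this bias would vanish. Limited time on drug among late starters is not counted here as a separate bias, since it is part of what a timing contrast compares.

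**Conclusion.** The concern holds in a limited form. The subanalysis defines both groups by treatment after baseline and, read literally, leaves never-users unplaced. If they are left out and later start follows insufficient response, the later group is selected for poor response. Under the assumed rates and no true effect this is worth about 3 to 15 points in favour of early use (2.9 to 12.5 by hand, 3.2 to 14.5 in the simulation), of which about 2 to 11 survive stratification on baseline severity. The upper part of that range is material beside the 25-point target difference.

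Because confounding by severity may pull the other way, the net sign cannot be predicted. A positive, null or negative result would be equally hard to read as an effect of early use. The figures illustrate the mechanism and do not forecast this cohort. The point concerns a subanalysis, and the primary outcome and the minimum of 535 patients do not rest on it, so the severity is moderate.

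**What to change.** Replace the contrast with a 3-month landmark comparison. Among patients still in follow-up at 3 months, compare those who started an immunomodulator or biological before 3 months with those who had not started by then, counting later and never users together, on 1-year remission. Report Crohn's disease and ulcerative colitis/IBD-unclassified separately. Adjust or weight for initial activity score, age, localisation, behaviour or extension, and country or centre. Include induction therapy only where it is not itself the early immunomodulator or biological; otherwise the model would adjust for the exposure.

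The cost is analysis-plan wording. The article already provides for activity scores and detailed treatment information at fixed time points. One downside is that the estimate becomes that of a strategy, starting early versus not starting early, because the comparator mixes later and never users. A second limit should be stated with the result: the near-zero bias in step 3 used true severity, so residual confounding will remain to the extent that measured baseline factors capture it incompletely, or that starts within the first 3 months respond to early course.
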